### Project B1

#### Background and hypotheses

In study B1, it is hypothesized that the strategy of motor re-mapping after injury of the primary motor cortex M1 of the hand will mainly depend on the extent and severity of Wallerian degeneration of the pyramidal tract. Only in subjects who show some preservation of M1 will TMS be associated with a return of dexterity at 6 months [10,55,56]. Contra-lesional recruitment of secondary motor areas in the non-involved hemisphere after stroke is considered to reflect compensation strategies that are enhanced by application of modified CIMT, compared to those victims who receive conventional care. In line with this hypothesis, it is further expected that (persistent) recruitment of corresponding contra-lesional secondary motor areas, including primary (M1) cortex, supplementary motor cortex (SMA), cingulate cortex (CC) and dorsolateral (dPMA) and ventral pre-motor areas (vPMA), beyond 4 weeks will be associated with poor quality of upper limb recovery and high use of compensation strategies. Accordingly, it is expected that patients demonstrating normalization of upper limb function will show a concomitant reduction of contra-lesional cortical activation on fMRI and a shift of activation back to the original M1, SMA and PMA areas of the affected hemisphere. In those patients who fail to show substantial recovery to normal, compensatory recruitment of the non-affected hemisphere will persist. In line with this hypothesis, we assume that early applied modified CIMT will be associated with a predominantly increased ipsi-lesional recruitment of activity of M1, SMA, dorsal and ventral PMA when compared to those patients who received the control treatment. Higher lateralization indexes will then be found in volumes of interest (VOI's). Therefore, low impairment recovery profiles and high compensatory movement strategies i.e., bending and rotating the trunk in a standardized reaching task, are expected to be positively associated with contra-lesional activity patterns and low lateralization indexes. Contrastingly, patients exhibiting behavioural normalization of upper limb performance in the standardized reaching task will show focusing of activity towards the physiologically recruited areas i.e., M1, SMA and PMA as VOI' s in the ipsi-lesional hemisphere, after a possible initial recruitment of contra-lesional areas.

#### Design

fMRI data will be acquired with a Philips ACS-NT 1.5 tesla clinical scanner, using the blood oxygen level-dependent (BOLD) sensitive, navigated 3D PRESTO pulse sequence [57]. Parameter settings will be: TE (echo time) 35 ms, TR (repetition time) 24 ms, flip angle 9 degrees, FOV (Field of View) 180 × 225 × 91 mm, matrix 52 × 64 × 26, voxel size 3.51 mm isotropic, scan time per fMRI volume 2.4 seconds. Following the fMRI procedure, an anatomical scan will be acquired with a slice thickness of 1.2 mm. Although fMRI does not allow direct measurement of neural activity, activation-induced BOLD signal changes occur in agreement with known functional topography. fMRI measurements will be obtained as soon as patients are able to extent their wrist beyond 10 and their fingers beyond 20 degrees. The second and third measurements will be made at the fifth week and at 6 months post stroke. In the fMRI experiments, 3 different motor tasks, in blocked design (active extension of wrist and fingers, passive extension and imaginary extension) will be executed in random order. First, the fMRI protocol will be applied in 5 healthy, age-matched subjects. Before fMRI scanning, patients will be trained to perform active extension movements with the wrist and fingers, using a wrist-hand orthosis which will guarantee a correct movement in the flexion-extension direction. In addition, the same movement will be executed passively and as an imaginary movement during the fMRI scanning. Before each fMRI study, EMG silence will be controlled during a sham fMRI training session using biofeedback electrodes attached to the extensors and flexors of the paretic and non-paretic hands. A metronome will be used to maintain the 0.3 Hz rhythm. Activation patterns will be analysed with statistical Parametric Mapping (SPM2) software. Voxels will be considered active if the task-related t-value exceeds 4.0, corresponding to p < 0.05, Bonferroni-corrected for the total number of voxels in all VOI's. Preliminary results from a 42-year-old healthy subject are shown in Figure 3. The fMRI scanning time is estimated to take about 50 minutes.

**Figure 3 F3:**
[figure not shown]
**a-d Illustration of the orthotic hand-device for B1, fMRI project (Figure 3a)**. Preliminary results from a 42 years healthy subject are shown in figures 3b-d. First, the subject was asked to perform the motor extension paradigm actively (Figure 3b). Similarly, 10 runs of 10 passive movements were executed by pushing the orthotic device manually (Figure 3c). Finally, the subject was asked to perform the task imaginary with the same block design, while keeping both arms relaxed (Figure 3d).

To control for the severity of motor deficit of the corticospinal tract (M1) in the involved and non-involved hemispheres, Motor Evoked Potentials (MEP) will be recorded within the first days post stroke and will be repeated 6 months after. The mechanisms of Transcranial Magnetic Stimulation (TMS) – induced changes in muscle activity (using a Magstim 200 stimulator) have been shown to involve both direct corticospinal and transsynaptic projections. The intensity of stimulation will be slowly increased until the stimulation induces visible muscle twitches in the bellies of the abductor digiti minimi muscle and biceps brachii muscle [58]. These muscles will be regarded as representative of proximal and distal motor functions in the upper extremity. Additionally, extensors of wrist and fingers (i.e., mm. extensor carpi radialis longus and mm. extensor digitorum) will be tested. Bipolar electromyographic (EMG) recordings will be obtained from pairs of surface electrodes using a Nicolet Viking or Oxford Synergy electromyograph [59-61]. The amplitude, latency and area under the curve will be used to quantify the MEP. In addition, MEP parameters i.e. motor thresholds and silent periods as a reflection of intracortical inhibition found on the paretic side will be compared with those on the non-paretic side as well as with 10 healthy age- and gender-matched controls [62].

### Project B2

#### Background and hypothesis

There are strong indications that motor recovery after cortical injury occurs to a large extent through behavioural compensation strategies [10,36,63]. These can be considered to be potential confounders in our understanding of 'neural repair' and related cerebral recovery after stroke [10,36]. For example, in one recent study of stroke patients, moderately to severely impaired subjects used compensatory strategies of the trunk to accomplish a pointing task, rather than trying to achieve restitution of the original arm function [25,64]. Cortical changes detected by fMRI may therefore reflect alternative (compensatory) motor skill learning rather than restoration of representations lost due to the infarct or the non-use of the limb. As a result, these studies failed to differentiate between 'true motor recovery' and 'compensatory motor recovery'. This has caused considerable difficulty in the interpretation of such changes in fMRI studies, apart from other potential confounding factors such as a lack of control over mirror movements, strength, precision and the timing of imaginary movements (motor paradigm) during fMRI scanning.

#### Design

The performance of the upper limb will be assessed using a standardized reaching task. Measurements will start as soon as the patient is able to execute the reaching task on the ARAT. Measurements will be repeated weekly until the fourth week post stroke, and at 8 and 26 weeks post stroke. One 10 cubic cm block weighing 200 g will be positioned on the top of an ARAT box in front of the subjects, at eye level. Patients will be asked to pick up the block with the paretic arm while sitting in front of the ARAT box. The distance between block and body will be standardized by taking subject's arm's length as the maximum reaching distance. Subjects will be asked to keep their trunk positioned against the back of their chair during the reaching task. However, if the reaching task cannot be performed, compensatory bending of the trunk will be allowed. At the start of each attempt, the patient's hand rests on a pressure-sensitive switch which is positioned on the floor of the ARAT box. The event of picking up the block will be registered by another pressure-sensitive switch, which is positioned under the block on the ARAT box. Each reaching task will be executed in a preferred and comfortable manner by the patient and will be repeated at least 10 times. Between attempts, one minute of rest will be inserted in order to prevent fatigue. Kinematics will be measured using a 6 Degrees Of Freedom electromagnetic tracking device (Polhemus Liberty, Polhemus, Vermont, USA), capable of separately assessing trunk, shoulder, elbow and finger positions and rotations. Bending of the trunk and rotation of the shoulder towards the object will be regarded a indicator of compensation. Interjoint cross-correlation coefficients will be used as a reflection of synergistic dependent and independent movement control of the upper limb [64,65].

### Project B3

#### Background and hypotheses

Project B3 will investigate the relationship between CNS function and parameters describing end-point neuromechanics. It is likely that the absence or presence of corticospinal tract as established by TMS, as well as cortical reorganization as established by fMRI will go with higher joint stiffness, impaired motor function i.e. paresis and control i.e. inappropriate reflex settings or modulation. In parallel with the expected negative correlation between regaining dexterity on the one hand and persistent cortical reorganization and the absence of corticospinal tract (as established by TMS) on the other, it is hypothesized that a high degree of stiffness, paresis and absence of reflex modulation will be related to poor outcome. The longitudinal relationship between cortical and neuromechanical parameters is expected to elucidate whether peripheral neuromechanics are an independent variable in stroke recovery.

#### Design

Neuromechanics will be assessed under both passive and active conditions, using haptic robots ("Wristalyzer", Moog FCS Inc., Nieuw Vennep, The Netherlands). These are powerful, force controlled manipulators by which force- and position perturbations can be applied in a precise way to human joints while reactions of the subject in terms of forces and joint angles can be measured [30]. To apply torque perturbations, a haptic controller is used which replaces the dynamics of the real manipulator with virtual dynamics, in this case an (rotational) inertia-spring-damper system. This means that to the subject the manipulator i.e. the external environment 'feels' like a mass-spring-damper system (haptic is Greek for 'touch sense'). Previous research showed that under an active posture task primarily the negative signs of post stroke limb dysfunction dominate, i.e. the paresis component and the absence of optimal adaptation of reflexes to the environmental conditions, which is normally found [26,29,31]. As the spinal reflex loop is under control of the higher brain areas, it is likely that the peripheral spinal reflex loop properties and therefore endpoint mechanical joint behaviour is related to integrity of the corticospinal tract and the amount of reorganization of cortical brain areas. Loss of corticospinal tract integrity and persistent CNS reorganization is anticipated to be related to high joint stiffness, loss of motor function i.e. paresis and absence of reflex modulation. This combination is labelled an unfavourable cluster, while in the favourable cluster, opposite findings are linked to corticospinal tract integrity and absent or disappearing cortical reorganization. Distinguishing these clusters and their dynamics as a function of elapsing time after stroke and their relationship to upper limb function will be a significant step forward in understanding the effect of primary cortical damage on peripheral motor function. By studying the effect of CMIT and EMG-NMS, it can be estimated whether these clusters can be modified by interventions. For project B3, parameters will be measured repetitively in a cohort of N = 30 patients with an unfavourable prognosis, of which N = 15 patients will receive additional EMG-NMS therapy and N = 30 with a favourable prognosis, of which N = 15 patients will receive additional modified CIMT therapy.

### The C project

#### Background and hypothesis

The aim of project C of EXPLICIT is to discover the longitudinal association between the time-dependent cortical changes revealed by fMRI and TMS (project B1), observed changes in kinematics (project B2) and observed changes in neuromechanics (project B3) on the one hand and the improvements in dexterity found during the first 6 months after stroke on the other. This final project hypothesizes that relatively poor recovery profiles in terms of neurological deficits (FM-score, MI-arm score, somatosensory deficits and neglect) and ARAT are significantly positively associated with: 1) the use of compensation strategies expressed as bending and rotating the trunk towards an object, 2) the amount of contra-lesional activation in fMRI and TMS i.e., recruitment of cerebral activity and 3) high joint stiffness, persistent paresis and impaired reflex modulation. Those patients showing a normalization of ARAT outcome i.e. > 53 points are expected to show: 1) normalization of kinematics, 2) focusing i.e. reduction of cortical activity on the original physiological areas involved and intactness of corticospinal tract on TMS and 3) normalisation of joint stiffness, motor function and control.

#### Design

The dynamics i.e. longitudinal associations will be identified by applying a first-order autoregressive random coefficient model. This statistical model of change scores enables exploration of the quasi-causal relationships between improvements in upper limb function on the one hand and neurophysiological changes (project B1), changes in body functions (including kinematics, project B2) and body structures (including neuromechanics; project B3) on the other. The random coefficient analysis will be performed with MLwin version 2.02. [66]. The iterative generalized least-squares algorithm will be used to estimate the regression coefficients. Before conducting the random coefficient analysis, the changes between successive measurements of the time-dependent covariates will be calculated and plotted to check for compliance with model assumptions. Because time constitutes an independent covariate, random coefficient analysis enables longitudinal analysis of unequally spaced time points of measurement, and is able to deal with missing values. To investigate the possible longitudinal association between upper limb function and potential covariates, bivariate longitudinal regression analysis will initially be conducted, including ARAT change scores and time-independent covariates at baseline, such as age, gender, and lateralization of stroke, as well as one time lag change scores of the time-dependent covariates such as MI-arm, Fugl-Meyer arm and LCT, as well as change scores on the laterality index of VOI in fMRI and TMS change scores. Subsequently, standardized regression coefficients will be calculated, and a multivariate regression model to predict functional recovery of dexterity based on ARAT scores will be developed. The likelihood ratio test will be used to evaluate the need to allow random regression coefficients into the model, whereas the Wald test will be used to obtain a P value for a particular regression coefficient. (See for recent examples [67,68])

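### Project C says its model deals with missing values, but kinematic and, to a lesser extent, fMRI covariates are unmeasured until the arm recovers, so the association holds only for patients able to do the task

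*Protocol article*

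**What the plan says.** The C project, Design, names the model: "The dynamics i.e. longitudinal associations will be identified by applying a first-order autoregressive random coefficient model". ARAT change is the response. The explanatory side holds "one time lag change scores of the time-dependent covariates such as MI-arm, Fugl-Meyer arm and LCT", together with "change scores on the laterality index of VOI in fMRI and TMS change scores", and the same section places kinematic change (project B2) among the processes to be related to upper limb improvement. On incomplete data it says only that "random coefficient analysis enables longitudinal analysis of unequally spaced time points of measurement, and is able to deal with missing values". It does not separate outcomes from covariates and states no assumption about why values are missing.

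Two measurement rules make the first covariate value depend on recovery:

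- Project B2, Design: "Measurements will start as soon as the patient is able to execute the reaching task on the ARAT". Recording is then weekly to week 4, and at weeks 8 and 26. The rule is softened: "if the reaching task cannot be performed, compensatory bending of the trunk will be allowed".
- Project B1, Design: "fMRI measurements will be obtained as soon as patients are able to extent their wrist beyond 10 and their fingers beyond 20 degrees". Later scans are fixed at week 5 and 6 months.

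The C project, Background and hypothesis, expects relatively poor recovery profiles to go with "the use of compensation strategies expressed as bending and rotating the trunk towards an object" and with more contralesional activation.

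**The concern.** A random coefficient model fitted by iterative generalised least squares is conditional on its covariates. If the response is missing at some visits and that missingness depends only on what has been observed, the fit remains valid. If a covariate change score is missing, the row has nothing to enter and is dropped. The model does nothing to recover it.

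Here the dropped rows are not a random set. They are the visits at which the arm could not yet reach or extend, so availability is governed by function that ARAT itself measures. The hypothesis concerns poor recovery, and the programme regards the first month as decisive; those are where the data thin out. A reader relying on the protocol's statement would take the fitted association to describe all the patients studied.

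**Working it through.** The protocol gives no sample size, power or missingness rate for project C, so there is no stated figure to reproduce. The check sets the rules against the model and then illustrates the consequence.

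**1. Kinematic intervals available.** A change score needs two measured occasions. I assume the weekly series begins at week 1, giving occasions at weeks 1, 2, 3, 4, 8 and 26.

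| First able at week | Usable change intervals (of 5) |
|---|---|
| 1 | 5 |
| 2 | 4 |
| 3 | 3 |
| 4 | 2 |
| 8 | 1 |
| 26 or never | 0 |

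**2. fMRI intervals available.** Three scans give at most two change scores per patient, or 2 × 30 = 60 in all. If the first scan is at week w, the first interval lasts 5 − w weeks: 4 weeks at w = 1, 1 week at w = 4, and none if the threshold is not met before week 5. The second interval, 26 − 5 = 21 weeks, does not depend on the threshold. The A projects section requires at least 10 degrees of wrist and finger extension for A1 at the end of week 1, against more than 20 degrees at the fingers for the scan. So the usual effect is a delayed baseline and a first interval whose length depends on recovery.

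**3. Effect on the slope (illustrative; all inputs assumed).** I simulated 200,000 patients with starting function averaging 12 ARAT points (SD 8), recovering over the six occasions. ARAT change was regressed on compensation change with interval effects. Ordinary least squares stood in for the planned model. Compensation was unobserved until a noisy threshold of function was passed.

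| Threshold (ARAT points) | Intervals lost | Slope ratio (observed rows / all rows), association constant | Slope ratio, association differs below and above 15 points |
|---|---|---|---|
| 5 | 6% | 0.97 | 1.14 |
| 10 | 15% | 0.97 | 1.25 |
| 15 | 28% | 0.97 | 1.30 |
| 20 | 45% | 1.01 | 1.35 |

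In the last column, compensation rises with ARAT below 15 points and falls with it above. The constant case shows almost no bias because selection acts on function at the start of an interval, whereas the response is the later change. Bias appears only when the association differs across the threshold. If the association were instead steeper below the threshold than above it, the observed slope would be too shallow.

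**4. Who is measured.** Recruitment for the B projects lists kinematics for 30 A1 patients and only TMS and haptic robotics for 30 A2 patients. The Abstract gives kinematics to 60 patients from A1 and A2. The difference matters. Power analysis for project A2 puts regaining some dexterity (ARAT above 9) at about 6% under usual care, with an assumed difference of 12%. Take that as absolute (18%), take the 15 and 15 split in Project B3, Design, and assume that ability to reach roughly coincides with ARAT above 9. Then 15 × 0.06 + 15 × 0.18 = 0.9 + 2.7 = 3.6 of 30 A2 patients would ever be measurable. Trunk-assisted reaching below that score would raise the number. A further illustrative run, also on assumed inputs, gave slope ratios of about 0.98 to 1.19 for A1-like and 0.96 to 1.76 for A2-like patients.

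**The case against.** The strongest counter-argument is that no bias has been shown. That is largely right about size and sign. A reader might infer that the slope must shrink towards zero, by analogy with truncating a bivariate normal distribution on the outcome. With the lowest share p of recovery unseen, c the normal quantile of p, λ = φ(c)/(1 − p) and v = 1 + cλ − λ², the slope ratio is v/[1 − r²(1 − v)]. At p = 0.20, v = 0.583, giving 0.62 (r = −0.4) and 0.69 (r = −0.6). At p = 0.40, v = 0.422, giving 0.47 and 0.53. The arithmetic is sound but belongs to a cross-sectional regression on recovery level. Project C models change scores, where the illustration gave a ratio near 1 or above it. The shrinkage reading is not supported.

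Nor may a reader infer that all poor recoverers are excluded. Trunk bending is allowed, so patients who reach by compensating are recorded; only those who cannot reach even so are lost. The fMRI threshold governs the first scan alone, so fMRI is the weaker half of the point. A1 entry limits it further, although the numbered inclusion list for A1 omits the extension criterion.

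It is also fair to say that trunk bending during a reach is undefined, rather than missing, in someone who cannot reach. This stands, and it is the reason to define the association as conditional on ability.

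The last argument is that missing-data handling belongs in an analysis plan, and that project C is exploratory. Silence would indeed be no finding. But the article makes a positive claim about the model, and for these covariates the claim is wrong.

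**Conclusion.** The statement on missing values is too broad. It covers missing ARAT outcomes under missing at random. It does not cover kinematic covariates, nor, to a lesser extent, fMRI covariates, whose first measurement depends on recovery. What project C can estimate is the association among patients already able to perform the task, which need not equal the association implied for poor recovery profiles.

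The documents fix neither the direction nor the amount of any difference. The 0.97 to 1.35 range above rests on assumed recovery curves and thresholds. A constant association would make the issue nearly harmless, but constancy cannot be presumed when restitution versus substitution is the programme's own open question. Loss of data is probably modest if kinematics are confined to A1 and much larger if A2 is included. The A1 and A2 treatment comparisons on ARAT are not affected.

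**What to change.** - Limit the sentence in the C project, Design, to missing ARAT outcomes under missing at random.
- Define the kinematic and fMRI associations, and the conclusions drawn from them, as conditional on ability to perform the task.
- Use the ARAT and extension data already collected to analyse ability (yes/no) by visit alongside the conditional model. Report time to first measurement and the number never measurable. For fMRI, report the length of the first interval.
- Reconcile the Abstract with Recruitment for the B projects on whether A2 patients have kinematics.
- Do not fill impossible visits with the worst observed compensation value. That gives low-function visits high compensation by construction and so builds in the association under test.

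The cost is a narrower claim and a little more analysis. With about 30 patients, the ability analysis should be kept simple.
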